#### 2.6.2. Qualitative Analyses

The qualitative data about the impact of the prevention programmes on health and well-being of community members, gathered during the focus groups, interviews and observations, will be transcribed and analysed using the qualitative data software programme MAXQDA (https://www.maxqda.com/, accessed on 8 February 2023). In order to account for subjectivity and personal errors, two researchers will be coding and analysing the data. We will determine which aspects of community members’ health, well-being, social and daily life are linked to participation in the prevention project by conducting an initial explorative content analysis, determining themes, followed by a more in-depth thematic content analysis. Observations and memos made during interviews about any contextual information (e.g., atmosphere) will be discussed between the interviewers and coders.

The analyses for the process evaluation, with the aim of determining effective elements, will be focusing on the observational data and data from focus groups and interviews with DN and community members. This analysis, as well as the analyses of DN’s motivation for and perspective on preventive work will be performed in the same way as described above.

### 2.7. Ethics

This study was reviewed and declared not subject to the law on research involving human subjects by the Institutional Review Board of the Medical Ethical Committee Leiden-Den Haag-Delft for observational studies and was registered under number WSC-2022-10. The protocol is currently under review for compliance with scientific due diligence. Prior to participation in this study, participants will be informed about the goal, procedures, confidentiality of data and other relevant information both orally and in writing. They are then asked to sign an informed consent form for the specific parts of the study that they will participate in. Results and conclusions from the collected data will be given back to Buurtzorg anonymously and will be used to adjust aspects of this study and future prevention projects where necessary. Data will be stored securely on a server at the Leyden Academy on Vitality and Ageing. Randomly generated codes will be assigned to the data, making sure that no personal data can be traced back to responses on questionnaires, interviews or other collected data. These codes are stored in a key separate from the data files and safeguarded through data protection measures. The key can only be accessed by the researcher and two coordinators of this project. The handling of data will comply with the EU General Data Protection Regulation and the Dutch Act on Implementation of the General Data Protection Regulation.

## 3. Discussion

The primary objectives of the described study in this article are (1) to study how collective prevention programmes in community-based healthcare, mainly focused on older people, affects participants’ health and well-being and (2) to evaluate and clarify what it takes for DN to develop and implement such programmes in collaboration with community members. This identifies required skills, knowledge and other essential elements during the programme’s development and implementation. A secondary objective is to gather information about how DN view prevention as a part of their job and what motivates them to work on preventive care. The results of this study will contribute to the discussion of how preventive care fits into our healthcare system in order to make it more suitable for an ageing population. Since a large part of the population encounters the same lifestyle-related health problems at later age, partly due to influences of the environment they live in, this collective approach adapted to the local context is reasoned to be more effective on the long term than healthcare strategies that mainly focus on the individual. Moreover, the fact that this study involves 14 different locations, with variations in number of inhabitants, socio-economic status and urbanity, provides opportunities to compare health effects and effective elements of collective prevention in different contexts.

### 3.1. Implications

This study will provide information about which aspects of health, well-being and social life are affected by different collective prevention projects. As community members will be working together to organise activities, we expect that the impact of the prevention projects for community members will initially be measurable with our social effect measures. Initial participation may be a difficult step for many people, but once people are part of a group, it will be easier to take the initiative of going to other activities or outings in their daily life. This is expected to prevent or decrease loneliness and increase social participation, which has been shown to increase health and well-being [5,48,49]. The relations between people should be carefully considered and monitored to avoid negative effects on well-being due to failure of support, neglect or misdirection, which could lead to outcomes such as increased distress or decreased self-worth and self-efficacy [50]. The goal is to form a local social network with people helping and motivating each other and contributing to collective health goals by making use of each other’s talents. Ultimately, this may also lead to a decreased need for long term care or certain home care tasks. A stronger social network will also mean that people likely have better access to and knowledge of the available support systems and services, which will eventually lead to decrease in the workload of DN. This may contribute to better health care for the entire ageing population, because more people are able to maintain good health for a longer time with no or minimum help from DN. Consequently, DN can help more people without increase in the work hours.

All the prevention projects will be focused on a health-related issue or concern that Buurtzorg teams have identified together with community members. Therefore, this project is expected to improve health in the community. After identifying successful elements in the programme and viable projects, it could be implemented in other locations. It is a particular ambition of the study to use the lessons learned to implement collective prevention in all Buurtzorg teams (N = 950) in the Netherlands. Finally, the project aims to provide evidence for effective and sustainable bottom-up health care for other home care organisations and contributing to future-proof health care systems that fit an ageing population.

The development and implementation process can be time consuming for DN and will include tasks that normally lie outside the scope of their daily work. Therefore, we expect to encounter unforeseen difficulties and challenges along the way. It may also lead to fluctuations in work satisfaction during the project. The population of DN in this study is highly motivated to work on prevention, so we expect that their work satisfaction will eventually increase once the prevention projects are well underway. The effect of motivation patterns on success will also be studied, which can be used as a guideline or criterion for starting a prevention project in a certain team of DN.

We also aim to shed light on other working elements such as required skills, knowledge and appropriate steps to take when organising a collective prevention project. As we expect community engagement to be an important factor in each projects’ success, we will compare our results with the conceptual model for community engagement and pay special attention to elements such as organizational partnerships and alliances [51]. While these partnerships are not specifically assessed in this project, we acknowledge their importance and would suggest more detailed investigation on this topic for future steps of this project. We aim to create a general timeline and guidelines to make implementation of collective prevention programmes possible on a broader scale.

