## 2. Materials and Methods

### 2.1. Population

The study population in this Collective Prevention project will consist of two groups: DN and community members. The DN are all employees of community healthcare organisation Buurtzorg. Buurtzorg has created a model of care in which self-managing teams of 6–12 nurses deliver all the care that a patient needs. They help people get ready in the morning, wash them, give medication, but also provide medical care such as wound treatment. The teams try to involve the formal and informal networks of their patients to sustain independency for as long as possible. The teams organize their work together and share the workload and responsibility for the quality of care. Buurtzorg has invited all interested teams to apply for the current project by submitting their motivations to work on prevention in their work area. The whole team needs to be on board with the project and they are made aware that they will spend roughly 8 hours a week on the project. The motivations and capabilities of the teams were assessed during an interview. At the time of writing, 18 Buurtzorg teams, from 14 different localities all over the country, are selected to participate. These localities vary in number of inhabitants (1230–19,400), mean income (€26,000–€40,000) and urbanity (1–5) on a scale from 1 (most urban: >2500 addresses per km^2^) to 5 (least urban: <500 addresses per km^2^) [42]. The target population of the collective prevention projects consists of the 55+ population in the neighbourhoods under study. The only strict inclusion criterium for this study is that the participants live in one of the neighbourhoods under study and participate in the project in the neighbourhood on a regular basis. DN will be responsible for recruitment of this study population through interviews and networking in their locality, for which they will receive training and tips during workshops led by the researchers. Participation in both the prevention project and this study is voluntary and, therefore, we work with a convenience sample. Given the range of localities we aim for a diverse population in terms of sex, civil status and income. We expect to involve approximately 25–30 community members per site, amounting to a total of 350–420 individuals in our community sample.

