#### 2.4.2. District Nurses

##### Job Satisfaction and Motivation

The impact on job satisfaction of the DN will be evaluated using a selection of 17 out of 77 questions from the standard annual Buurtzorg job satisfaction questionnaire (see Supplementary Materials, Questionnaire S2). This selection contains the questions that are most relevant to job satisfaction in relation to this project. The DN of the participating Buurtzorg teams who have a key role in the development of the prevention project will complete this questionnaire once every year. We will also obtain mean scores on these 17 items of Buurtzorg employees who do not participate in the study. This will provide us with a control measure, so we can compare the change over the course of this study between the involved nurses in our programme and those involved in regular care of Buurtzorg. Similarly, we will collect data that Buurtzorg has on mean hours of care per client to track the changes during our project and compare the participating teams with regular teams.

The researchers will conduct individual semi-structured interviews in the first and last year of the project to gather information about DN’s views on preventive care, their motivations to work on prevention, the relation to community care and their view on the prevention project in their team. We will ask questions such as “How does prevention fit into the work of DN according to you?”, “How was the subject of prevention represented in your education and how does this relate to your current view on prevention?”, “Can you name some positive and some less positive aspects of your team’s collective prevention project?” (see Supplementary Materials, Topic list S2). These interviews will be followed by focus groups with each Buurtzorg team with a topic list that transpires from the outcomes of the individual interviews. Topics that are likely to be discussed are different views on prevention, representation of prevention in education, roles in and views on the Collective Prevention programme and collaboration within the team. Prior to these interviews, we obtained informed consent from the DN.

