### 3.2. Limitations

This study will take place in 14 different localities with prevention projects that are designed for that specific context. This makes the projects relevant for the neighbourhood, but also comes with challenges in generalisability and comparing the prevention projects and their health and social effects. For example, the effects could be different for different ethnic groups due to underlying differences in views and perceptions regarding health, social norms and collective prevention. This should be taken into account if prevention projects are deployed in more localities. Additionally, the participating Buurtzorg teams are not selected at random, but they apply for participation in the project and are selected based on a strong motivation and willingness to work on prevention. This means that the sample of district nurses in this project likely already has a certain set of characteristics or values that are different from a randomized sample. It should, therefore, be noted that the implementation of collective prevention programmes in all Buurtzorg teams may shine light on new challenges or required skills and knowledge that may have been taken for granted in the selected sample of the current study. Furthermore, it is difficult to accurately measure prevention, as the desired outcome is a non-event. In addition, there is no control group in this study and we can only compare with general population outcomes. Furthermore, we are not able to control for the effect of planning and organizing a project in a community. Structural Governance and Collective Empowerment are two practices in community-based participatory research that influence the outcomes through interaction with the context, relationships and other aspects of the research [52]. This means that the health and social effects that we will measure cannot only be attributed to the content of the prevention project. Finally, results in this study will mainly be based on a population of relatively older people, since they are more likely to have the time to help organise such a project. Whereas collective prevention should be focused on all ages, as this is the best way to collectively change our lifestyle and prevent age-related diseases. This may be a next step for spreading the prevention projects of this study.

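### Every team was selected for strong motivation, so the study cannot support a motivation-based criterion for starting projects in other teams

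*Protocol article*

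**What the plan says.** Section 3.1 (Implications) describes the nurses in the study: "The population of DN in this study is highly motivated to work on prevention". It then announces a use for the motivation findings: "The effect of motivation patterns on success will also be studied, which can be used as a guideline or criterion for starting a prevention project". The unit meant is the individual nursing team.

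Section 2.1 (Population) explains how teams entered:
- by application: "Buurtzorg has invited all interested teams to apply for the current project by submitting their motivations to work on prevention in their work area"
- with full team commitment: "The whole team needs to be on board with the project"
- after screening: "The motivations and capabilities of the teams were assessed during an interview"

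The result is that "18 Buurtzorg teams, from 14 different localities all over the country, are selected to participate". Section 3.2 (Limitations) confirms the rule. Teams were not drawn at random; instead "they apply for participation in the project and are selected based on a strong motivation and willingness to work on prevention".

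Motivation is then studied by interview, under Job Satisfaction and Motivation in section 2.4.2: "The researchers will conduct individual semi-structured interviews in the first and last year of the project to gather information about DN’s views". The subject of those views is preventive care. The same interviews cover the nurses' motivations and their opinion of their own team's project, including its better and worse sides. Section 2.6.2 assigns the motivation material to thematic content analysis.

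**The concern.** Motivation has two roles here. It is the filter through which teams enter, and it is also the explanatory factor whose effect on success is to be studied. A criterion for starting has to separate teams that should begin a project from teams that should not, and that requires seeing how projects fare on both sides of the line. Here one side is empty by design.

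A second, smaller difficulty is timing. One of the two rounds of individual interviews falls in the last year. By then nurses know how their project went, and they talk about it in the same interview as their motivation. A link between motivation and success drawn from that round could reflect success colouring the account of motivation.

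What is at stake is how the findings are used. If the successful teams share a kind of motivation, this could be passed on as a condition for starting elsewhere. If no kind stands out, motivation could be taken to be unimportant. Neither conclusion would be warranted for teams unlike those studied.

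**Working it through.** The plan attaches no sample-size or power figure to this question, so there is nothing to reproduce. The check sets the passages side by side.

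1. **What the claim needs.** Section 3.1 speaks of a guideline or criterion for starting in a given team. The unit is therefore the team. The evidence required is project success in teams that do and do not meet the criterion.

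2. **What enters the sample.** Section 2.1 applies three filters: the team applies and states its motivations, the whole team backs the project, and motivation and capability are assessed at interview. Section 3.2 sums this up as selection on strong motivation. Of the 18 teams, all passed and none lies below the entry level.

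3. **Whether outside data fill the gap.** Sections 2.4.2 and 2.6.1 bring in Buurtzorg staff who do not take part, but only for mean scores on 17 job-satisfaction items and for mean hours of care per client. These staff supply neither motivation data nor a project that could succeed or fail.

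4. **What contrast remains.** Motivated teams can differ in why they are motivated. Contrasts of that kind can be described across 18 teams in 14 localities. They apply to teams that volunteer and pass the same entry assessment. More teams recruited by the same rule would not change this, because the missing region would stay empty.

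5. **Whether the limitation covers it.** Section 3.2 warns that roll-out to all teams may bring up new challenges, or skills and knowledge that the selected teams already had. It does not mention the motivation criterion, so the statement in section 3.1 stands unqualified.

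6. **Which motivation data precede the outcome.** Applications and selection interviews come before the project, and first-year interviews come at its start. Last-year interviews come after nurses know how the project has gone. Section 2.2 adds that qualitative measures help decide which projects count as successful, so last-year accounts could inform both sides of the comparison.

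**The case against.** The strongest reply is that the sentence concerns patterns of motivation, not its level, and that the analysis is qualitative. Teams that are all highly motivated can still differ in kind, and a thematic comparison of kinds is legitimate. This stands, and it marks out what the study can deliver. It does not rescue a criterion for teams that never volunteered.

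The reply continues that the selection is openly disclosed and that nurses' motivation falls under a secondary objective. Both are true, and both limit the weight of the point. The disclosure still leaves the stated use untouched.

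On timing, the article does not say that last-year interviews will be related to success, and first-year interviews are already planned. The concern is therefore a risk to close off, not an error already made.

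A reader might infer two stronger things:
- **That the result will decide which of Buurtzorg's 950 teams may start a project.** The documents do not say so. Section 3.1 says only that the finding can be used in this way, and its stated ambition is implementation in all teams, not gating them.
- **That selection will shrink a correlation between motivation and success by some calculable amount.** The plan has no motivation scale, correlation or test. It also does not give the number of applicants, so any such figure would rest on assumptions from outside the plan.

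**Conclusion.** The point holds in a limited form. The article offers a start criterion that its design cannot support, because no project outcome is observed in teams with ordinary or low motivation. The study can at most generate hypotheses about kinds of motivation among motivated volunteer teams.

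The gap is one of design and cannot be expressed as a number beyond the count: 18 teams within the selected range and none outside it. The conclusion assumes that selection worked as sections 2.1 and 3.2 describe, and that the criterion is meant for teams beyond those that would apply and be selected in the same way. The primary objectives and the analyses of community members' outcomes are unaffected. The change is worth making because the sentence could steer later roll-out and is easily corrected.

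**What to change.** 1. **Section 3.1.** Replace the statement that the motivation findings can guide or decide whether a team starts. Say instead that they will yield exploratory hypotheses applying to self-selected, highly motivated teams, and that a start criterion would need data from teams with a wider range of motivation.

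2. **Sections 2.4.2 and 2.6.2.** State that the comparison of motivation with project success will use motivation recorded before success is known. That means first-year interviews, together with applications and selection interviews where these are available and may be used for research. Use last-year interviews only to describe how views changed.

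The cost is a less favourable claim and a little more coding, since the early material is already planned or may already be held. No new data collection is needed and no objective is lost.

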### 3.2. Limitations

This study will take place in 14 different localities with prevention projects that are designed for that specific context. This makes the projects relevant for the neighbourhood, but also comes with challenges in generalisability and comparing the prevention projects and their health and social effects. For example, the effects could be different for different ethnic groups due to underlying differences in views and perceptions regarding health, social norms and collective prevention. This should be taken into account if prevention projects are deployed in more localities. Additionally, the participating Buurtzorg teams are not selected at random, but they apply for participation in the project and are selected based on a strong motivation and willingness to work on prevention. This means that the sample of district nurses in this project likely already has a certain set of characteristics or values that are different from a randomized sample. It should, therefore, be noted that the implementation of collective prevention programmes in all Buurtzorg teams may shine light on new challenges or required skills and knowledge that may have been taken for granted in the selected sample of the current study. Furthermore, it is difficult to accurately measure prevention, as the desired outcome is a non-event. In addition, there is no control group in this study and we can only compare with general population outcomes. Furthermore, we are not able to control for the effect of planning and organizing a project in a community. Structural Governance and Collective Empowerment are two practices in community-based participatory research that influence the outcomes through interaction with the context, relationships and other aspects of the research [52]. This means that the health and social effects that we will measure cannot only be attributed to the content of the prevention project. Finally, results in this study will mainly be based on a population of relatively older people, since they are more likely to have the time to help organise such a project. Whereas collective prevention should be focused on all ages, as this is the best way to collectively change our lifestyle and prevent age-related diseases. This may be a next step for spreading the prevention projects of this study.

